#### Control

HFNC (Optiflow™ nasal high-flow interface) driven by AIRVO 2 humidification system (Fisher and Paykel).

Interventions will be initiated at the time of randomisation and both the Helmet CPAP and HFNC will be applied and titrated according to local best standard of care (SOC). Hereby, HFNC will be started at a flow of 30 L/min with a possibility to increase flow to maximum 60 L/min at the choice of the attending physician (corresponding PEEP ~ 3–5 cmH_2_O [12]). Helmet CPAP will be started at a flow of 40 L/min and a PEEP of 5 cmH_2_O which can be increased to a maximum of 20 cmH_2_O at the attending physician’s discretion. We suspect that the PEEP will normally be used at around 8–10 (− 12) cmH_2_O. The study provides no guidelines on fraction of inspired oxygen (FiO2%) or litres of oxygen per minute. Oxygen settings will be titrated according to the attending physicians’ choice. Local SOC guidelines recommend a target SpO2 of 92%. When patients allocated to the intervention needs to take off the helmet for short periods of time (e.g. for meals), they will generally be put on HFNC according to physician’s choice. Included patients who require transportation from the medical COVID-cohort to the ICU for mechanical ventilation will be put on a portable HFNC during transportation between wards and prior to intubation according to the wishes of our local intensivists. Extubated patients will also be put on HFNC regardless of treatment allocation according to the wishes of our local intensivists. We believe that these circumstances will only have a moderate effect on the primary outcome because we expect the time from transportation to intubation to be short and we expect the number re-intubations within 28 days to be few.

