#### Outcomes rational

Based on the best current evidence [4, 9], we expect any difference in efficacy between intervention and control to be due to a difference in intubation rate and/or possibly time in respirator rather than survival. Respirator use is a particularly clinically relevant outcome during the current COVID-19 pandemic when ICU beds are scarce. The benefit of choosing VFD as a primary outcome rather than intubation frequency is that VFD strongly penalises death. Hereby, VFD effectively assesses our primary concern for harm related to the intervention, namely, an adverse delay to intubation leading to reduced survival. The drawback of VFD is a potential dilution of harm (death) due to high efficacy (intubation rate) which is why we are also including days alive within 28 and 180 days as secondary outcomes. The 180 days mortality outcome will not be reported in the primary manuscript because we do not wish to delay dissemination of findings, but we consider it necessary to evaluate since many patients with COVID-19 have prolonged hospital stay. SpO2/FiO2 ratio is included as a sort of proof of concept outcome with the purpose of confirming or rejecting our underlying assumption that the higher PEEP enabled by the Helmet CPAP will improve lung aeration. We also have a patient-centred outcome regarding self-reported comfort. Both devices are reported to have superior tolerance compared to low-flow oxygen therapy and CPAP masks but they have never been tested head-to-head in adults. Device comfort may be particularly important if the trial does not show superiority or if the effect size is small. Lastly, we have included a secondary outcome on carbon dioxide rebreathing which, according to our judgement, is the main harm apart from death and comfort/tolerance issues that can be considered more likely for the intervention group than the control group. We are taking measure to avoid this from happening (i.e. minimum Helmet CPAP air flow 40 L/min).

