### Data management {19}

Screening and baseline data will be entered live using an eCRF at the time of randomisation. Further data on primary and secondary outcomes will be entered into the REDCap database collectively after all patient recruitment has finished, using filled-out paper CRFs and electronic health records. Individual patient data will be handled as ordinary chart records and will be kept according to the European General Data Protection Regulation (GDPR). All original records (e.g. consent forms and CRFs) will be retained at the Department of Infectious Disease in Helsingborg Hospital for 15 years to allow inspection by relevant authorities. The coded trial database will be maintained for 15 years if requested for revision.

**Table 1 Tab1:** Data collection flow chart

Timing	Method	Data type and specification
At screening	eCRF (RedCap)	Inclusion and exclusion criteria and informed consent
At randomisation	eCRF (RedCap)	Allocation, treatment limitations (i.e. ICU admission), weight, height, place of birth, smoking, date of symptom start, gender, clinical frailty scale, mode of respiratory support, SpO2%, litres O2/min, RR/min and NEWS
One hour post randomisation	CRF paper	SpO2/FiO2-ratio
24 h post randomisation	CRF paper	Patient comfort (visual analogue scale (VAS) 1–10)
Daily for 28 days	CRF paper	Mode of respiratory support, number of hours per 24 h in allocated support, nr of hours in prone position per 24 h, NEWS, PEEP or Flow, SpO2%, RR/min and events with commentary (e.g. allocation violation, death, exit from study, ICU admission or hospital discharge)
Retrospectively from electronic medical charts	eCRF (RedCap)	Comorbidities, vitals, medications, radiology, microbiology and laboratory parameters at triage, randomisation and during hospital stay, and, duration of hospital stay, duration of ICU stay, duration of mechanical ventilation and days alive within 28 and 180 days, respectively.

*Abbreviations*: *eCRF* electronic case report form, *ICU* intensive care unit, *SpO2%* peripheral oxygen saturation, *L O2/min* litres of oxygen per minute, *RR* respiratory rate, *NEWS* national early warning score, *FiO2* fraction of inspired oxygen, *PEEP* positive end-expiratory pressure

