### Adverse event reporting and harms {22}

The Swedish Medical Products Agency (Läkemedelsverket) has reviewed the study design in May 2020 and concluded that it should not be considered a clinical trial in the traditional sense but rather a pragmatic randomised study between two approved medical devices. Hence, reporting of adverse events will not be as ambitious as a clinical trial testing a novel drug. We will aim to evaluate any harm from the intervention in our primary and secondary endpoints on survival, intubation frequency, carbon dioxide rebreathing and patient-reported comfort. There is also a commentary section in the study-specific CRFs where study nurses can report allocation violations or any unexpected side-effects from allocated intervention.

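### Barotrauma (pneumothorax or pneumomediastinum) is not a prespecified harm outcome and would be captured only incidentally, with no count or comparison by arm planned

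*Protocol article*

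**What the plan says.** **Pressure.** Under Intervention description {11a}, Control, HFNC is said to correspond to a PEEP of about 3–5 cmH2O. Helmet PEEP starts at 5 cmH2O, "which can be increased to a maximum of 20" cmH2O. The authors expect usual values of about 8–10 (–12) cmH2O.

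**Entry.** Eligibility criteria {10} exclude pneumothorax and, separately, a venous pCO2 above 6 kPa.

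**Harms.** Adverse event reporting and harms {22} aims to evaluate any harm from the intervention through the "primary and secondary endpoints on survival, intubation frequency, carbon dioxide rebreathing and patient-reported comfort". It adds a CRF comment section where "study nurses can report allocation violations or any unexpected side-effects from allocated intervention". The rationale for the outcomes states that carbon dioxide rebreathing "is the main harm apart from death and comfort/tolerance issues that can be considered more likely for the intervention group". Neither section mentions air leak or pressure injury.

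**Data collected.** Table 1 under Data management {19} lists retrospective chart extraction of "Comorbidities, vitals, medications, radiology, microbiology and laboratory parameters at triage, randomisation and during hospital stay". It also lists a daily CRF entry for "events with commentary (e.g. allocation violation, death, exit from study, ICU admission or hospital discharge".

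**The concern.** A higher PEEP is the mechanism under test: the outcomes rationale says the SpO2/FiO2 outcome is there to check whether the helmet's higher PEEP improves lung aeration. A harm that could plausibly follow from the same pressure difference has no outcome of its own.

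The only side-effect route named in {22} is optional and worded for unexpected events. A nurse who regards an air leak on positive pressure as a known possibility could reasonably leave it out. The nurses also know the allocation ({17a}), so optional comments may be made more readily in one arm than in the other.

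At stake is how well a statement about helmet harms could be supported. An air leak managed without intubation or death would register in none of the four named harm measures, except perhaps comfort if it was present at 24 h. One that led to intubation would be counted as an intubation and nothing more. The protocol plans no interim analysis {21b}, no data monitoring committee {21a} and no auditing {23}, so no other planned process would bring an imbalance to light.

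**Working it through.** The point is mainly textual. The plan states no barotrauma figure, so there is none to reproduce.

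**1. The two entry exclusions, followed through the plan**

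| Condition excluded at entry {10} | Outcome {12} | Harm measure {22} | Analysis {20a} |
|---|---|---|---|
| pCO2 > 6 kPa in venous blood | Yes, same threshold, within 28 days | Yes | Chi-squared or Fisher's exact test |
| Pneumothorax | None | None | None |

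The first condition returns as a defined outcome with a planned comparison. The second does not appear again after entry.

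**2. Where an air leak could be recorded**

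- Comment section in {22}: optional and worded for unexpected side-effects.
- Daily event field in Table 1: open-ended, with examples that do not include air leak.
- Chart radiology in Table 1: covers the hospital stay, but is tied to no outcome.

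The information may therefore exist in the trial data. What is missing is a definition, a uniform search in both arms and a planned tabulation.

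**3. Size of the pressure difference, from the figures in {11a}**

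- Expected use: 8/5 = 1.6 to 12/3 = 4 times the HFNC value.
- Permitted maximum: 20/5 = 4 to 20/3 = 6.7 times.

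The first range describes usual use as the authors foresee it. The second applies only at the ceiling.

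**4. How many events might occur (illustration only)**

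The assumed risk p in the helmet arm is 1% to 10%, with n = 60 from Sample size {14}. Expected events are 60p. The chance of at least one event is 1 − (1 − p)^60.

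| Assumed p | Expected events | Chance of at least one |
|---|---|---|
| 1% | 0.6 | 45% |
| 2% | 1.2 | 70% |
| 5% | 3 | 95% |
| 10% | 6 | 99.8% |

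**5. Would a test be useful?**

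Normal approximation, two-sided 0.05, 60 per arm: power = Φ[(|p2 − p1| − 1.96·SE0)/SE1]. Here SE0 = √[2p̄(1 − p̄)/60], SE1 = √{[p1(1 − p1) + p2(1 − p2)]/60}, and p̄ is the mean of p1 and p2.

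- 1% v 5%: SE0 = 0.0311, SE1 = 0.0309. (0.04 − 0.0610)/0.0309 = −0.68, so power is about 25%.
- 2% v 10%: SE0 = 0.0434, SE1 = 0.0427. (0.08 − 0.0850)/0.0427 = −0.12, so power is about 45%.

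The approximation is rough at such low counts, but it is enough to show that a significance test would say little. Uniform counting is what adds information.

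**The case against.** The strongest reply is that this was a disclosed and reasoned choice. {22} says adverse event reporting will be less ambitious than in a trial of a new drug, citing the regulator's view and the use of two approved devices. {18a} explains why prospective data are kept to a minimum. The authors judged rebreathing to be the main additional harm, and the documents give no barotrauma rate to contradict them. The criteria give no reason for excluding pneumothorax, so linking that exclusion to helmet pressure is an inference. This is also a condensed article with CRFs available on request, and the coding of chart radiology could be settled there.

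Much of this stands. It rules out several stronger readings that a reader might adopt:

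- **That air leaks would go uncounted altogether.** Table 1 collects radiology during the stay and has an open daily event field. The events may be recoverable.
- **That leaks found after transfer to intensive care would be lost.** {11b} expects follow-up to continue after such a move, and chart extraction spans the hospital stay.
- **That the helmet arm runs at 4 to 6.7 times the HFNC pressure.** That holds only at the permitted maximum. The expected range gives 1.6 to 4.
- **That no events in 60 would bound the risk at 4.9%.** That bound needs every patient to be a known negative. With clinically ordered imaging, patients not imaged are not known negatives, so the figure should not be quoted.
- **That the trial sets out to declare the helmet safe.** Its stated hypothesis is fewer intubations without a negative effect on survival.

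The reply does not remove the core point, which does not rest on silence. {12} and {22} list the outcomes and harm measures, and {22} fixes the reporting wording. A later tabulation cannot recover comments that nurses were not invited to make. The less ambitious reporting that the authors defend is compatible with one defined item drawn from charts already being reviewed.

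**Conclusion.** The point holds in a limited form. Followed as written, the plan yields no defined count of pneumothorax or pneumomediastinum and no comparison by arm. Its side-effect wording discourages reporting of a foreseeable event. Capture would be incidental, not absent.

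No stated figure changes, and neither the primary analysis nor the sample size is affected. The consequence is confined to the harm evaluation: the protocol's aim of evaluating any harm from the intervention is wider than its listed measures can deliver. On assumed risks of 1% to 10%, between 0.6 and 6 events would be expected in the helmet arm, so the gain is a sound descriptive count and not a test. The conclusion assumes that air leak is a foreseeable harm of positive pressure. That is a reviewer's judgement; the documents neither state nor deny it. No view is taken on the pressure limit.

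**What to change.** 1. In {12} and {22}, add a descriptive safety outcome: pneumothorax or pneumomediastinum on any clinically ordered imaging within 28 days of randomisation.
2. Extract it in the same way in both arms from the chart radiology already listed in Table 1. Table 1 covers the hospital stay, so state how imaging after discharge but before day 28 is handled.
3. Report counts with 95% CI by arm, the number of patients imaged in each arm, and whether each event came before or after intubation. Plan no formal test.
4. In {22}, replace the restriction to unexpected side-effects with any side-effects, expected or unexpected.

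The cost is one more field in an extraction already planned and one wording change, with no new imaging, visits or staff. The limitation is that imaging may be ordered more often in one arm, and patients not imaged cannot be taken as free of the event. That is why the number imaged must be reported beside the counts.

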### Frequency and plans for auditing trial conduct {23}

We have no plans for auditing trial conduct in this investigator-initiated pragmatic trial.

### Dissemination plans {31a}

We plan to publish the trial results in a peer-reviewed medical journal.

## Discussion

We had three practical concerns during the planning stages of the trial in April and May 2020. First was the adequate supply of Helmet CPAP devices. Our local supplier’s stock was small and there was an export ban from Italian manufacturers during April. The ban was eventually lifted on the 11th of May 2020. Second was the feasibility of prone position in patients on the Helmet CPAP. Awake proning seems to be beneficial in COVID-19 and should optimally be available to both treatment groups [22]. In early May, Italian researchers published data to support the rational and feasibility of combining the Helmet CPAP and prone positioning without reports of harm [23, 24]. Third was the number of COVID-19 patients requiring intermediate-level care in our institution. At the time of writing, local COVID-19 incidence seems to have plateaued at a low to moderate level. This indicates that patient recruitment may take considerably longer than initially predicted from April forecasts [15]. Performing the trial at additional centres would naturally have been of benefit from recruitment and validity aspects. However, no other hospital in our region have prior experience from using the Helmet CPAP and we did not regard international cooperation as feasible, or reasonably quick to arrange, during the ongoing pandemic. The single-centre design and modest sample size is an important limitation and we acknowledge that small but clinically important differences may be missed.

## Trial status

Protocol version 1.0, 18 June 2020

Recruitment began on Wednesday 3 June 2020.

The first patient was recruited on 18 June 2020.

Recruitment is planned to be completed during the first half of 2021.

## Abbreviations

AHRF: Acute hypoxaemic respiratory failure
HFNC: High-flow nasal cannula
NIV: Non-invasive ventilation
PEEP: Positive end expiratory pressure
CPAP: Continuous positive airway pressure
ARDS: Acute respiratory distress syndrome
VBG: Venous blood gas
SpO2: Peripheral oxygen saturation
pCO2: Carbon dioxide partial pressure
VFD: Ventilator-free days
FiO2: Fraction of inspired oxygen
ICU: Intensive care unit
NEWS: National early warning score
eCRF: Electronic case report form
RR: Respiratory rate
